#### Surface roughness assessment

Surface roughness of the two groups will be compared using the independent *t* test. A *p* value of < 0.05 will be considered statistically significant.

#### Microbiological monitoring

The mean counts (× 10^5^) of individual bacterial species and the percentage of the total DNA probe will be calculated initially for each implant, then per subject and averaged across patients between groups. Periodontal pathogens include *P. gingivalis*, *Fusobacterium nucleatum* subspecies, and *P. intermedia*, among others. The proportions for the species will be distributed into the six complexes and an “other” group, as proposed by Socransky et al. [27]. Differences in microbiological parameters between groups will be identified using the Wilcoxon signed-rank test. Adjustments for multiple comparisons [28] will be performed when the bacterial species are evaluated simultaneously. The level of significance will be set at 5%.

Alpha and beta diversity analyses will be performed using Primer7 software and the QIIME2 microbiome bioinformatics platform [29, 30]. Alpha diversity, Shannon’s diversity index of both species number and distribution, Margalef’s index of numbers, and Pielou’s index of evenness of distribution [31–33] will be analyzed, and the significance of the differences between groups will be derived using the unpaired Student’s *t* test. Beta diversity analysis includes visualization of data at multiple taxonomic levels, with unweighted and weighted UniFrac distance metrics in order to generate PCoA plots [34]. Analysis of similarity (ANOSIM) will be performed to determine whether there are significant differences in microbial communities between groups. White’s non-parametric test will be applied to test for differences in the abundance of specific microbiota between the groups, with a false discovery rate cutoff of 0.005 with the use of STAMP [35].

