**Methods:**

The proposed study is designed as a 5-year randomized controlled trial. We plan to enroll 44 edentulous (mandible) patients seeking full-arch, fixed, implant-supported prostheses. The participants will be randomly allocated to one of two groups: group 1, in which the participants will receive zirconia frameworks with ceramic veneering, or group 2, in which the participants will receive titanium frameworks with acrylic resin veneering. Ten follow-up examinations will be completed by the end of this 5-year trial. Mucosal conditions around the implants will be recorded every 6 months after restoration. Peri-implant submucosal plaque will be collected at each reexamination, and bacteria flora analysis will be performed with 16S rRNA gene sequencing technology in order to compare differences in microbial diversity between groups. One week before each visit, periodontal maintenance will be arranged. Each participant will receive an X-ray examination every 12 months as a key index to evaluate the marginal bone level around the implants.

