##### Processing of microbiological samples

Bacterial identification and classification will be determined by sequencing of the V1 and V3 regions of the 16S rRNA gene and amplification by polymerase chain reaction (PCR), as well as library preparations, library quality inspections, and quantifications of DNA samples of the oral flora. The identified TAG sequences will be used for sample differentiation. Qualified libraries will be sequenced with the Hiseq 2500 high-throughput sequencing platform (Illumina, Inc., San Diego, CA, USA). Paired-end reads obtained by Hiseq/Miseq sequencing will be spliced into one sequence and the target sequence subjected to quality control filtering. The filtered sequence will be compared with a reference database, and the chimeric sequence will be removed to obtain the final optimized sequence. Operational taxonomic unit (OTU) cluster analysis and species classification annotations are based on optimized sequences, diversity index analysis is based on OTU clustering results, and species structure and difference analyses are based on taxonomic information. Beta diversity analysis, principal co-ordinate analysis (PCoA), and linear discriminant analysis (LDA) effect size analysis will be used to compare differences in microbial diversity and in significant microbial species between the two treatment groups.

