### Sample size

The sample size has been calculated with NCSS-PASS software. At 5 years, peri-implant bone loss in metal-resin/metal-ceramic IFCDPs was 0.9 ± 0.4 mm and peri-implant bone loss in ceramic IFCDPs was 0.6 ± 0.1 mm [26]. In the proposed study, the criterion for significance is set at *α* = 0.05 (type I error) and *β* = 0.10 (type II error). The analysis is two-tailed. Assuming a dropout rate of 20%, in order to determine if there is a difference in the degree of bone loss between the two groups, 22 cases per group and 44 cases in total will be required. A previous study included 20 edentulous subjects who received two mandibular implants [10]. The abutments were either titanium or zirconium dioxide (non-submerged implant placement, within-subject comparison, left-right randomization). After 3 months, mean absolute counts of *Porphyromonas gingivalis* of the titanium vs. zirconia abutment were 1,000,000 ± 0 vs. 64,000 ± 36,770, respectively. However, the difference between groups was not evaluated in this study. Mean absolute counts (mean) for *Prevotella intermedia* of the titanium vs. zirconia abutment were 600,088 ± 952,117 vs. 3,600,089 ± 804,935, although the difference between the two groups was not evaluated. In this study, the criterion for significance will be set at *α* = 0.05 (type I error) and *β* = 0.10 (type II error). The analysis will be two-tailed. Assuming a dropout rate at 20%, in order to determine if there is a difference in the amounts of *P*. *gingivalis* and *P. intermedia* between the two groups, three patients per group and six patients in total will be required.

In summary, the total sample size will be 44 (22 per group).

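### The species-level results are defined as counts (×10^5) and a percentage of total DNA probe, two variables that the described 16S sequencing assay cannot supply

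*Protocol article*

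**What the plan says.** **Endpoint.** Under Statistical analysis, Microbiological monitoring, the Protocol article gives two species-level variables. Mean counts in units of 10^5 "of individual bacterial species and the percentage of the total DNA probe will be calculated initially for each implant", then summarised per patient and averaged within groups. The same paragraph adds: "The proportions for the species will be distributed into the six complexes", plus a remainder group.

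**Assay.** The abstract states that "bacteria flora analysis will be performed with 16S rRNA gene sequencing technology". Processing of microbiological samples describes PCR amplification and sequencing of 16S rRNA regions, joining of paired reads, quality filtering and chimera removal. It continues: "Operational taxonomic unit (OTU) cluster analysis and species classification annotations are based on optimized sequences", and "diversity index analysis is based on OTU clustering results, and species structure and difference analyses are based on taxonomic information". The one quantification step it mentions stands in a list of library steps: "library preparations, library quality inspections, and quantifications of DNA samples of the oral flora".

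**Sample size.** The species calculation takes absolute counts of *P. gingivalis* and *P. intermedia* from an earlier 3-month abutment study. It aims to detect a difference in their amounts and arrives at 3 patients per group.

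**The concern.** The endpoint and the assay do not match. Amplicon sequencing yields, for each sample, a number of quality-filtered reads assigned to each taxon. The read total is set by library preparation and sequencing depth, not by how many bacteria were on the paper points. A count in units of 10^5 needs a quantitative assay, and a percentage of total DNA probe needs probes. The article describes neither.

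An analyst following the text would have to substitute something. The section names *P. gingivalis*, *F. nucleatum* and *P. intermedia* as pathogens of interest, so the choice affects results that clinicians will read. If raw reads were used, depth differences between samples would add noise to the species comparisons. A statement that one material carries more of a pathogen would have no support, because a species' share can change while its amount does not, and the reverse. Leaving the substitute open also allows raw or relative data to be chosen after results are seen, in a trial with interim analyses at 1 and 3 years.

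**Working it through.** **1. Stated variables against what the assay yields**

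| Item in the analysis text | What it requires | Available from the described sequencing? |
|---|---|---|
| Species counts (×10^5) | Calibrated quantity per species | No |
| Percentage of total DNA probe | Probe-based assay | No |
| Proportions by complex | Share of reads per species | Yes, as relative abundance |
| Alpha diversity, UniFrac/PCoA, ANOSIM | OTU table | Yes |
| LDA effect size, White's test in STAMP | Taxon abundances | Yes |

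**2. The plan's own species sample size**

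Inputs, all from Sample size: two-sided α = 0.05, power 0.90, dropout 20%.
- *P. intermedia*: 600,088 (SD 952,117) on titanium, 3,600,089 (SD 804,935) on zirconia
- *P. gingivalis*: 1,000,000 (SD 0) on titanium, 64,000 (SD 36,770) on zirconia

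Formula per group, normal approximation: n = (s1² + s2²)(z0.975 + z0.90)² / δ², with (1.960 + 1.282)² ≈ 10.51.
- *P. intermedia*: δ = 3,600,089 − 600,088 = 3,000,001. n = (952,117² + 804,935²) × 10.51 / 3,000,001² = 1.81, so 2 per group. With dropout, 2 / (1 − 0.2) = 2.5, so 3.
- *P. gingivalis*: δ = 1,000,000 − 64,000 = 936,000. n = 36,770² × 10.51 / 936,000² = 0.02, so 1 per group. With dropout, 1 / 0.8 = 1.25, so 2.

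The larger value is 3 per group, 6 in total, as stated. (With a t-based calculation *P. intermedia* needs 4 per group, or 4 / 0.8 = 5 with dropout.) Every input is an absolute count. The article gives no proportions or SDs on the relative scale, so no corresponding n can be computed there.

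**3. If raw reads replaced counts (depths assumed; the article gives none)**

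Reads for a species = share × depth. At a 5% share:
- 20,000 reads: 0.05 × 20,000 = 1,000
- 40,000 reads: 0.05 × 40,000 = 2,000
- 80,000 reads: 0.05 × 80,000 = 4,000

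The spurious ratio between two samples equals the ratio of their depths: 1 at equal depth, 2 or 4 in these examples.

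**4. Why shares do not measure amount (loads assumed)**

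500,000 / 10,000,000 = 5% and 50,000 / 1,000,000 = 5%. A tenfold difference in amount leaves the share unchanged.

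**The case against.** **Most of the microbiological analysis survives.** A reader might infer that no pathogen comparison can be run. The article does not support that. White's test, with a false discovery rate cutoff, compares the abundance of specific taxa; LDA effect size looks for distinguishing species; and the complex proportions can be read as relative abundance. The microbiological primary outcome is diversity, which uses neither disputed variable. This objection stands in full.

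**Reads may never be presented as amounts.** Nothing in the article says raw reads will replace counts. That is an inference from the unit of 10^5 and from the sample size section's aim of comparing amounts. The fourfold figure rests on assumed depths and compares two samples, not two arms. The technician is blinded to sample source, so depth variation would be expected mainly to add noise, not to favour one material. This also stands, and it limits the consequence to a conditional one.

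**The article condenses a fuller protocol.** A quantitative assay might be described in the full document, so its absence here does not prove that none is planned. That is fair, and the fix allows for it. It does not remove the point: the article states both an assay and an endpoint, and the two disagree. The DNA quantification step does not bridge the gap, because it is listed among library steps and measuring DNA in a sample gives no count per species. The PCR mentioned under Randomization, allocation, and blinding appears only where the technician's blinding is described.

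**Conclusion.** The point holds in limited form. Two species-level variables, counts (×10^5) and percentage of total DNA probe, cannot be derived from the only assay described. This is wrong text, not missing detail. It rests on reading the abstract and Processing of microbiological samples as the complete account of the assay.

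Its reach is narrow. The diversity analyses, LDA effect size, White's test and the complex proportions as relative abundance can proceed. The total of 44 comes from the bone-loss calculation and does not depend on the species one. A reader might infer that the microbiological primary outcome or the trial size is undermined; neither follows.

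The consequence is conditional. If raw reads were used as counts, species comparisons would carry depth noise and could not support statements about bacterial amount. Its size in this trial cannot be given, because the article reports no depths. The 3 per group for species reproduces only on the absolute-count scale and says nothing about power for relative abundance.

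**What to change.** - In Statistical analysis, Microbiological monitoring, define each species and complex variable as relative abundance: the percentage of quality-filtered reads in that sample, computed per implant and then averaged per patient. Delete the counts in units of 10^5 and the reference to total DNA probe.
- Limit conclusions on species to relative abundance. If a quantitative assay is already planned, name it and tie the count variable to it.
- In Sample size, remove the species calculation or mark it as not applying to the sequencing endpoint. Rewording it in terms of relative abundance would be wrong, because its means and SDs are absolute counts. The total of 44 stays as set by bone loss.
- Do not use the plaque index as a stand-in for submucosal bacterial quantity. It scores plaque at the margin, whereas the samples are taken below it after supramucosal plaque has been removed.

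This needs no new patients or samples. It changes the endpoint wording and gives up one sample size justification. The scientific cost is that no claim about absolute pathogen amounts can be made unless a quantitative assay is in place.

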### Randomization, allocation, and blinding

The subjects will be randomly allocated to one of two groups according to the prosthetic materials: titanium framework with acrylic resin veneering (group 1) or zirconia framework with/without ceramic veneering (group 2). The allocation of patients will be randomized using computer-generated permuted block randomization with an allocation ratio of 1:1. Randomization will be performed by sealed envelopes that will be opened after final impressions are obtained.

Microbiota analysis will be blinded after assignment to the intervention groups. Each sample will have a number associated with an allocation sequence, as well as information pertaining to the dental position and acquisition time. The technician conducting the PCR analysis will be blinded to the source of the sample. Interim statistical analysis will be performed at 1 and 3 years after implantation of the final prostheses. Final statistical analysis will be conducted at the end of the trial with the analyst blinded to both patient allocation and the interim analysis results.

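### Species counts and proportions in two independent randomised groups are to be compared with the Wilcoxon signed-rank test, a paired test, and the quantities named do not match the assay described

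*Protocol article*

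**What the plan says.** On design, the section Randomization, allocation, and blinding states: "The subjects will be randomly allocated to one of two groups according to the prosthetic materials". The method is "computer-generated permuted block randomization with an allocation ratio of 1:1". Nothing in the article matches or pairs patients across arms.

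On analysis, the first paragraph of Microbiological monitoring (under Statistical analysis) takes mean counts in units of 10^5 and a probe percentage. It reduces them stepwise: "percentage of the total DNA probe will be calculated initially for each implant, then per subject and averaged across patients between groups". It then says: "Differences in microbiological parameters between groups will be identified using the Wilcoxon signed-rank test". Adjustment for multiple comparisons and a 5% level follow. The next paragraph treats alpha diversity differently: the "significance of the differences between groups will be derived using the unpaired" Student's t test. Community differences go to ANOSIM, and the abundance of specific taxa to White's test.

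On the assay, Processing of microbiological samples states: "Bacterial identification and classification will be determined by sequencing of the V1 and V3 regions of the 16S rRNA gene". Its outputs are described thus: "Operational taxonomic unit (OTU) cluster analysis and species classification annotations are based on optimized sequences". No DNA-probe assay is described anywhere.

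On sample size, the Sample size section bases the microbiology calculation on absolute counts of P. gingivalis and P. intermedia from an earlier study that compared materials within patients. It arrives at 3 per group.

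**The concern.** The signed-rank test ranks within-pair differences. It suits two measurements on one patient, or patients matched in advance. Here a zirconia patient and a titanium patient have nothing linking them. Anyone applying the sentence literally must invent a pairing, such as row order in the data file, and leave out any patient without a partner.

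At stake is the comparison of named periodontal pathogens and species complexes between materials. It belongs to the second study objective, and two of its species have their own sample size calculation. A result that depends on file order cannot be reproduced by a second analyst. If the test is instead changed quietly at analysis, the choice is made after data exist, and the first planned look is at 1 year.

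The data question is separate. If the laboratory delivers sequence reads and taxonomic assignments, a percentage of total DNA probe cannot be computed from them.

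**Working it through.** **1. Are there pairs?** The randomisation section gives each patient one material. The analysis paragraph reduces the data to one value per subject and compares groups. A within-patient reading (change over time) does not fit, because the sentence concerns differences between groups. A left-right design appears only in the earlier study cited under Sample size. The clinical, roughness and alpha-diversity t tests are all independent or unpaired. So there are no pairs.

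**2. The plan's own microbiology figure.** Inputs from Sample size: two-sided alpha 0.05, power 0.90, dropout 20%.

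- P. intermedia: difference 3,600,089 − 600,088 = 3,000,001. SD = √((952,117² + 804,935²)/2) = 881,603. n = 2 × (1.960 + 1.282)² × (881,603 / 3,000,001)² = 1.81, rounded up to 2. 2 / 0.80 = 2.5, rounded up to 3 per group.
- P. gingivalis: difference 1,000,000 − 64,000 = 936,000. SD = √((0² + 36,770²)/2) = 26,000. n = 0.02, rounded up to 1. 1 / 0.80 = 1.25, rounded up to 2.

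The stated 3 per group is reproduced by an unpaired two-sample formula (normal approximation), so the calculation is consistent with independent groups. At 3 per group the smallest possible exact two-sided p is 2/2³ = 0.25 for signed-rank and 2/C(6,3) = 2/20 = 0.10 for rank-sum. This does not bite at the planned 22 per group.

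**3. Will the arms be equal?** 22 × 0.80 = 17.6, so about 18 evaluable per arm at the assumed dropout. The section on withdrawal and missing data also excludes patients who report smoking and discards any visit preceded by antibiotic use within 3 months. Exact equality at each analysed visit would be a coincidence. For 18 against 17 the signed-rank routine returns an error.

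**4. What happens if the arms are equal and the pairing is arbitrary?** Simulated independent data; the distributions and shifts are assumptions.

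| Data | Per arm | Shift | Signed-rank | Rank-sum |
|---|---|---|---|---|
| Lognormal, log-SD 1 | 18 | none | 0.045 | 0.046 |
| Lognormal, log-SD 1 | 22 | none | 0.051 | 0.055 |
| Lognormal, log-SD 1 | 18 | 1.0 on log scale | 0.74 | 0.82 |
| Lognormal, log-SD 1 | 22 | 1.0 on log scale | 0.83 | 0.89 |
| Normal | 18 | 1 SD | 0.80 | 0.81 |

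Entries are the proportion of p-values below 0.05. A repeat of the normal case gave 0.78 and 0.80.

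Dependence on pairing, in one lognormal data set with 18 per arm: rank-sum gives a single p of 0.017. Over 5,000 random pairings of the same values, signed-rank p ran from 0.000008 to 0.15.

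**5. Quantity against assay.** Set side by side, the laboratory section yields reads, OTUs and taxonomic annotation. The analysis paragraph uses counts in units of 10^5 and a probe percentage. The sample size section uses absolute counts. Counts might be taken to mean reads, but a probe percentage cannot.

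**The case against.** The fair reply is that this is a slip in a test name. The other between-group t tests are unpaired, the sample size follows an unpaired formula, and nowhere does the article plan to pair patients or discard any. A competent analyst would use the rank-sum test. That is probably so, but the sentence as written names the wrong test and nothing else in the article corrects it.

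Three stronger readings are tempting, and the article does not support them.

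- *A primary outcome is tested wrongly.* The listed primary outcome is the diversity of submucosal species. Diversity goes to the unpaired t test and ANOSIM. The faulty sentence governs species counts and proportions, which are not listed as primary.
- *False positives are inflated, or a fixed share of results would flip.* Type I error is intact under arbitrary pairing. The share of pairings reaching 0.05 depends on the data set. Among normal data sets with rank-sum p between 0.036 and 0.046 it ran from 7% to 90%, and with rank-sum p between 0.005 and 0.015 its median was 99%. No single percentage describes the plan.
- *The adjusted 5% level and White's test at a false discovery rate of 0.005 contradict each other.* They belong to two separately stated analyses. Taxa may overlap, but which result takes precedence can be settled in an analysis plan that is not shown.

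On the assay, the article is condensed, and its laboratory section mentions DNA quantification in the same list as library preparation. A quantitative assay may have been left out. The mismatch is real, but the article does not show which side is wrong.

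**Conclusion.** The point holds, within limits. A paired test is named for two independent groups. It is undefined for unequal arms and depends on the pairing chosen for equal arms. The cost is an irreproducible p-value and some loss of power: about 6 to 8 percentage points under the assumed lognormal data and 1 to 2 under normal data. Error control is not lost. The power figures rest on the assumed distributions and shifts and illustrate scale only.

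The affected part is the species-level comparison of counts and proportions, including P. gingivalis and P. intermedia. Alpha diversity, ANOSIM and White's test stand as they are. The error itself leaves every stated sample size unchanged.

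The mismatch between the analysed quantity and the described assay is a second, separate inconsistency. It calls for reconciliation, not for a particular replacement.

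**What to change.** 1. In Statistical analysis, Microbiological monitoring, replace the signed-rank test by the Wilcoxon rank-sum (Mann-Whitney) test, applied to the one value per subject that the paragraph already defines. This changes wording only and needs no new data. It should be done before the 1-year interim analysis.

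2. Reconcile Processing of microbiological samples, Sample size, and the microbiology analysis paragraph, so that the analysed quantity is one the described assay produces. If absolute counts are intended, describe the assay that yields them. If sequencing-based quantities are intended, remove the probe percentage and restate the microbiology sample size justification on that quantity, because its present inputs are absolute counts. This costs more than a wording change: either a laboratory method has to be described or the calculation has to be redone. The planned total of 44 comes from the bone-loss calculation, not from the microbiology figure of 3 per group.

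### The species comparison between two independently randomised arms is assigned a paired test, the Wilcoxon signed-rank

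*Protocol article*

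**What the plan says.** In the protocol article, Statistical analysis, Microbiological monitoring, species counts and percentages are "calculated initially for each implant, then per subject and averaged across patients between groups". The next step is the test: "Differences in microbiological parameters between groups will be identified using the Wilcoxon signed-rank test". An adjustment for multiple comparisons across species follows, at the 5% level. The results concerned are those for *P. gingivalis*, *F. nucleatum*, *P. intermedia* and other pathogens, and for the six bacterial complexes.

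The design is given under Randomization, allocation, and blinding: "The subjects will be randomly allocated to one of two groups according to the prosthetic materials", by "computer-generated permuted block randomization with an allocation ratio of 1:1".

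For the alpha-diversity indices of the same two arms, the same Microbiological monitoring section says that "the significance of the differences between groups will be derived using the unpaired" Student's *t* test.

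**The concern.** The signed-rank test takes one difference per matched pair and ranks those differences. It needs a reason why a particular zirconia value belongs with a particular titanium value. Nothing in the design supplies one, so the test statistic is not defined by the data alone: someone has to invent a pairing first.

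The affected results are not marginal. Submucosal bacteria are the subject of the trial's title, and *P. gingivalis* and *P. intermedia* have their own calculation under Sample size. A multiplicity adjustment cannot repair p values that have no unique starting value. The interim analyses at 1 and 3 years would meet the same difficulty.

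**Working it through.** The protocol gives no figure on this point to reproduce. The check compares what the test needs with what the design provides, then illustrates the consequence.

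**1. Is there any pairing?**

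| Source in the protocol | What it implies |
|---|---|
| Study design and setting; Interventions | One mandibular prosthesis per patient, one material each |
| Randomization, allocation, and blinding | Permuted blocks, 1:1. Blocks balance numbers; they do not match individuals |
| Microbiological monitoring (statistical) | One averaged value per patient, so two independent sets of patient values |
| Clinical monitoring and X-ray assessment; Surface roughness assessment | Independent *t* tests for probing depth, X-ray indices and roughness in the same arms |
| Microbiological monitoring (statistical), alpha diversity | Unpaired *t* test in the same arms |
| Sample size | The only paired comparison described is in the cited earlier study, where both materials were placed in the same mouth |

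No matching, crossover or split-mouth feature is described. Three readings that might rescue the sentence fail:
- Change over time within a patient would be paired, but the sentence concerns differences between groups.
- Permuted blocks do not form patient pairs.
- Pairing the two group means species by species would make species the unit of analysis. That conflicts with the per-patient averaging and with the adjustment across species.

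**2. How often would the arms be equal in size?** Inputs from Sample size: 22 per arm, 20% dropout. Assumption: dropouts occur independently, so each arm's count is Binomial(22, 0.2).

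P(equal) = Σₖ [C(22,k) × 0.2ᵏ × 0.8²²⁻ᵏ]², k = 0 to 22, = 0.1505, about 15%.

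In the other 85% or so, the signed-rank test cannot use all patients; a standard routine given 18 versus 17 values returns an error. Under Withdrawal and missing data processing, visits that follow antibiotic use are discarded and patients who smoke are excluded, which adds further scope for imbalance at a given visit.

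**3. If the arms are equal, how far does p depend on the pairing?** The documents give no patient-level data, so the distributions below are assumptions. About 18 per arm remain after dropout (22 × 0.8 = 17.6).

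- *Borderline datasets.* Log-normal values, log-scale SD 1.5, log-scale shift 1.2, 18 per arm; 60 datasets with rank-sum p between 0.02 and 0.05; 300 random pairings each. Mean rank-sum p was 0.030. The signed-rank p had an average median of 0.068 and an average 95% range of 0.012 to 0.18, and 50% of pairings fell below 0.05.
- *Two single datasets, not selected on p.* Log-normal, log-scale SD 1, shift 0.6; 5,000 random pairings each:

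| Patients per arm | Rank-sum p | Signed-rank p, lowest to highest | Pairings with p < 0.05 |
|---|---|---|---|
| 18 | 0.003 | below 0.0001 to 0.154 | 66% |
| 22 | 0.149 | 0.003 to 0.290 | 38% |

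The dependence runs both ways: a clear rank-sum result can be lost, and a rank-sum p of 0.149 can become nominally significant.

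**4. Error rates if one pairing is fixed without regard to outcome.** 18 per arm, log-normal, log-scale SD 1, 4,000 datasets per setting:
- No effect: rejection 4.6% (signed-rank) versus 4.3% (rank-sum).
- Shift of 1 SD on the log scale: power 74% versus 81%.

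**The case against.** The strongest reply accepts that the test is wrong and disputes how much follows.

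- **Naming slip.** Since every other comparison of these arms is unpaired, signed-rank was probably written for rank-sum. That is plausible, but the protocol names a specific and different test, and correcting the name is the whole of the remedy. It is not a matter left to a later document, because a test is stated.
- **Another valid test is planned.** The same section applies White's non-parametric test to the abundance of specific microbiota. This stands as a limit on the claim: some taxa have a valid route to a p value. It does not correct the sentence on subject-averaged counts, percentages and complexes, which is where the p value is undefined.
- **The primary microbiological outcome is untouched.** Diversity is the listed primary outcome, and it is tested with the unpaired *t* test and ANOSIM. This is correct, although two of the species have their own sample-size calculation.
- **The borderline simulation is selective.** It keeps only datasets near the 5% boundary, where changing tests often changes the answer. Without that selection (18 per arm, log-scale SD 1.5, 3,000 datasets, one arbitrary pairing each), rejection under no effect is 4.8% for signed-rank and 4.3% for rank-sum, with 96% agreement. At a shift of 1.2, power is 53% versus 61%, with 83% agreement; on log values the power gap nearly closes (60% versus 61%). These figures stand. They show that the fault is not inflation of type I error, and they do not supply the missing pairing.

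**Conclusion.** The concern holds. The protocol specifies a paired test for a comparison of two independent groups, so the species analysis cannot be carried out as written. With unequal arms, the likely case at about 85% under independent 20% dropout, the test cannot use all patients. With equal arms its p value is not unique: among borderline datasets, half of the possible pairings fell on each side of 0.05.

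The absence of pairs and the dependence on their order follow from the design and from the test, and need no distributional assumption. The sizes quoted do rest on assumed log-normal data, and the 0.012 to 0.18 range applies only to borderline results. The harm is an undefined p value and some lost power, not a demonstrated excess of false positives. It is confined to the signed-rank analysis of species and complexes. It should be corrected before any data are analysed, including at the 1-year interim.

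**What to change.** In Statistical analysis, Microbiological monitoring, replace the Wilcoxon signed-rank test with the Wilcoxon rank-sum (Mann-Whitney) test, applied to one value per patient at each visit (the mean over implants that the section already derives). This gives a single p value whether or not the arms are equal in size. Keep the planned adjustment across species. Reserve the signed-rank test for changes within a patient between visits, if those are wanted.

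While the sentence is open, it would help to say how this analysis relates to White's test, which covers overlapping abundance data under a different threshold (a false discovery rate of 0.005), and to note that the stated adjustment covers species and not repeated visits. Neither point is needed for the correction itself.

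The cost is one sentence of analysis wording. Data collection and sample size do not change.
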